**Fig. 3 Fig3:**
[figure not shown]
Study sample

### Sample size

For study 1 we will recruit N = 600 youth and expect a participation rate of c. 70–80% after one year. Power is sufficient (1−β = 0.8) to detect small to medium effect sizes *f*^2^ of c. 0.08, applying multiple regression models including covariates and testing specific predictors, for a given β of 0.05. For the App based study 1 multilevel models are applied to carry out between-subjects analysis of covariance. Moderators will be included to test for the interaction effects between groups (LOC vs HCG) within the Cyberball task. We expect moderate to large effect sizes (d = 0.8) with sufficient power to detect significant effects given 1−b = 0.8 and a = 0.05 for study 2 with N = 60 youths, even when accounting for c. 13% dropouts. For study 3, mixed between and within-subjects analysis of covariance or linear mixed models are carried out. Based on our BEAT pilot trial (DRKS00014580), where a high effect size for within subject measures revealed (d = 1.37) a medium to high effect size for these effects can be assumed (f = 0.25, taking r = 0.5 for the correlation among repeated measures), the required sample size would be N = 34 with sufficient power to detect significant effects given 1−β = 0.8 and β = 0.05 for study 3 with N = 120 youths, even when accounting for dropouts. Exploratory epigenetic goals involve predictors and within-subject effects and are expected to be sufficiently powered if effect sizes are medium to large (Fig. 3 depicts the study sample).

### Recruitment

Recruitment efforts include media, posting on websites, contacting health care institutions and secondary, professional schools or Universities in the German speaking part of Switzerland [33]. In case of positive LOC scores or interest in study participation as part of the HCG, an online screening will be conducted and eligibility, diagnostic status, in and exclusion criteria will be verified (see Fig. 2). The first participant in study 1 is planned to be enrolled in March 2021.

### Procedure and interventions

#### Cyberball task in virtual reality (VR)

The procedure of the i-BEAT study is illustrated in Fig. 2. Each participant is eligible to take part at one, two or at each of the three studies.

Interested youth are provided with a link to participate in study 1 and if eligible invited to participate in the App based study 1, study 2 and/or 3. Study 2 takes place between 2 and 4 PM after a regular meal at home. Upon arrival at the VR Lab at the Department of Psychology, University of Fribourg, First, electrodes to measure HRV (biosignalsplux, https://plux.info/12-biosignalsplux) are placed and a photograph of the participants is taken. HRV will be assessed continuously during the whole experiment.

With respect to eye tracking, we will use an HTC Vive Pro Eye (2160 × 1200 pixel resolution, 110° field of view) with a built-in eye-tracker (Tobii) to display the VR scene and concurrently collect gaze direction data at a sampling rate of 60 Hz. Gaze rays in 3D space obtained for both eyes will be geometrically transposed to represent horizontal and vertical deviations from regions of interest (as introduced in [48]). The procedure results in a form of data representation which is comparable to that obtained in traditional stationary eye-tracking where gaze deviations are described along a screen’s x- and y-axes. This form of data representation allows to apply a drift correction if samples directed towards regions of interest exhibit a drift over time (e.g. caused by a gradual lowering of the HMD on the participant’s head). After removing data obtained during blinks, data from both eyes will be averaged. Gaze will be labeled as either resting on a conspecific’s face (if deviation to any of the two faces present in the scene is lower than two degrees visual angle) or elsewhere.

At the beginning of the preparatory phase (see Fig. 4), participants self-report their psychological well-being and complete questionnaires (see Fig. 2). They are introduced to the adapted Cyberball task [27] (developed using the Unity 3D Game Engine) based on our pilot BEAT study and are informed that they will play with 2 peers and are shown pictures of these peers. Then, the motor-inhibition task, the gSST is applied. After a training trial with the oculus rift VR headset and oculus touch controller (preparation phase), the Cyberball task starts. All participants are exposed to the exclusion condition first followed by the inclusion condition. The order of the conditions is kept secret. The psychological effects of experiencing exclusion are repeatedly assessed during the VR Cyberball task. Participants rate how excluded or ignored they felt (manipulation check) as well as the percentage of received ball tosses. During recovery phase (see Fig. 4), they receive instructions in the App based daily-life study and during the preparatory phase, buccal cell samples to measure DNAm of candidate genes are provided (see Fig. 2). DNA methylation will be assessed using targeted bisulfite sequencing. In brief, bisulfite treated DNA will undergo two rounds of PCR (1st round: amplification for specific target regions; 2nd round: introduce identifiers for individuals), and will be sequenced on a MiSeq platform. To capture possible medium-term effects as a result of ostracism, a short questionnaire will be filled-out by all participants on their way home via the daily-life App and participants are debriefed about the purpose of study 2.

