Hypotheses concerning (1) primary and (2) secondary outcomes in study 2:Exposure to the exclusion condition of the VR Cyberball task leads to greater social threat-related effects during and after the exclusion (lower HRV; increased negative/reduced positive affect, impairment of basic needs) and to a delayed recovery in youth with LOC compared to the HCG. Exposure to the exclusion condition of the VR Cyberball task leads to greater social threat-related effects during and after the exclusion (lower HRV; increased negative/reduced positive affect, impairment of basic needs) and to a delayed recovery in youth with LOC compared to the HCG.Exposure to the exclusion condition leads to higher values of body dissatisfaction and of urge to engage in disinhibited eating after the task and during recovery in youth with LOC compared to HCG.RS interpretation bias (underestimation of ball tosses while included, misinterpretation as being excluded during inclusion condition, negative evaluation of ambiguous social scenarios) is more pronounced in youth with LOC than in the HCG.Exposure to the exclusion condition leads to stronger pupillary dilation response, stronger hyperscanning (eye gaze), more closed hand posture, stronger aversion of social gaze (measured as gaze dwell time) in youth with LOC compared to the HCG.Youth with LOC show lower motor inhibition capacities indicated by longer SSRTs than the HCG during the gSST.The motor inhibition capacity group difference is especially apparent in the food stimuli condition of the gSST in the LOC group compared to the HCG.

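### In Study 2 inclusion always follows exclusion, so two of the three interpretation-bias measures cannot separate bias from a lingering exclusion reaction

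*Protocol article*

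**What the plan says.** The section on the Cyberball task in virtual reality fixes one sequence for everybody: "All participants are exposed to the exclusion condition first followed by the inclusion condition". It adds that "The order of the conditions is kept secret". It gives no inclusion-first group, no washout and no reason for the order. It says that the effects of exclusion are rated repeatedly during the task, and that participants report how excluded they felt and what share of the tosses they received.

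Three Study 2 predictions in the section Study aims and hypotheses bear on this:

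- Exclusion "leads to greater social threat-related effects during and after the exclusion", and it leads "to a delayed recovery in youth with LOC compared to the HCG".
- Exclusion leads to "higher values of body dissatisfaction and of urge to engage in disinhibited eating after the task and during recovery" in the LOC group compared with the healthy control group (HCG).
- Interpretation bias linked to rejection sensitivity (RS) is more pronounced in LOC than in HCG. Its components are "underestimation of ball tosses while included, misinterpretation as being excluded during inclusion condition, negative evaluation of ambiguous social scenarios".

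The Data analysis section names a between-subjects analysis of covariance with moderators for Study 2. Fig. 4, which shows the timing of the phases, is not reproduced in the text at hand.

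**The concern.** Nobody plays the inclusion game without having been excluded first. The article's own first Study 2 prediction is that this prior exclusion affects LOC youth more strongly and for longer. If that is true, LOC youth may enter the inclusion game more distressed than controls, and that alone could make them feel excluded or undercount tosses. The bias hypothesis could then be partly confirmed with no bias in how inclusion is read, and the two results would not be separate findings.

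A second, smaller issue concerns body dissatisfaction and urge to eat. The hypothesis attributes them to exclusion but places them after the task and during recovery. Since the task consists of exclusion and then inclusion, these ratings appear to follow the inclusion game. They would then reflect exclusion plus re-inclusion, which could weaken or change the effect that is claimed.

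**Working it through.** **1. The plan's own figure.** Inputs from Sample size: d = 0.8, power 0.80, alpha 0.05, about 13% dropout, N = 60. A two-sided test and equal groups are assumed, as neither is stated.

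- Two-sample t-test: 26 per group gives power 0.807. Then 2 × 26 = 52, and 52 / (1 − 0.13) = 59.8, so 60. This reproduces the plan.
- The normal approximation gives 25 per group, and 50 / 0.87 = 57.5, so 58.
- A one-sided t-test gives 21 per group, and 42 / 0.87 = 48.3, so 49, which does not match.

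The sample size is not in question.

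**2. What the inclusion-phase comparison estimates.** Let B be the true LOC–HCG difference in reading inclusion, R the LOC–HCG difference in the exclusion reaction, and λ the share of R still present in the inclusion ratings. Then

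observed difference = B + λR.

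Every participant has the same order, so the data hold no inclusion ratings with λ = 0 by design. Three features that might seem to help do not:

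- The control group does not cancel λR, because R is itself predicted to differ from zero.
- Concealing the order does not remove an order effect.
- A group-by-condition contrast is confounded with group-by-period.

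**3. Illustration of size.** Set B = 0, R = 0.8 (the general planning value, borrowed for this outcome) and n = 26 per group. The test has 50 degrees of freedom and noncentrality 0.8λ × √(26/2).

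| λ (assumed) | apparent d | chance of declaring bias at nominal 5% |
|---|---|---|
| 0 | 0 | 5.0% |
| 0.10 | 0.08 | 5.9% |
| 0.25 | 0.20 | 10.9% |
| 0.50 | 0.40 | 29.3% |
| 0.75 | 0.60 | 56.4% |
| 1 | 0.80 | 80.7% |

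No document gives a value for λ.

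**4. Which outcomes are affected.**

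| Outcome | Position | Consequence |
|---|---|---|
| Threat effects in the exclusion phase | First block | No carry-over from inclusion |
| Tosses and felt exclusion while included | Second block | B and λR not separable |
| Ambiguous scenarios | Timing not visible | Affected only if given after Cyberball |
| Delayed recovery | After the task, from the order of the text | Persistence is the target, but re-inclusion intervenes |
| Body dissatisfaction and urge | After the task and in recovery | Apparently exclusion plus re-inclusion |

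**The case against.** The timing of the ratings is in figures that are not shown, so a pause or a new baseline between the games cannot be ruled out. That stands. A pause would make λ smaller, but it would not supply inclusion ratings from participants who had not been excluded. It likewise stands that the placement of the body-dissatisfaction and urge ratings is inferred from the order of the text.

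The Background describes RS as a readiness to perceive real or imagined rejection, often linked to past and current adverse experience. Misreading inclusion after a real exclusion fits that construct, and the hypothesis does not claim to concern unprimed participants. This is a fair defence of the measure. It supports reporting the measure as perception of inclusion after exclusion, but not as a finding separate from the exclusion reaction.

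The magnitude is conjectural. The carry-over shares have no source, d = 0.8 was not set for perceived tosses, and at 10% carry-over the error rate is almost nominal. The direction could also reverse: inclusion might feel stronger by contrast with exclusion and hide a true bias. All of this stands, and for that reason the table is an illustration only.

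A reader might infer that carry-over also contaminates the delayed-recovery hypothesis, or that Study 2 as a whole is confounded. The documents support neither. Delayed recovery means that the exclusion reaction persists, so persistence is what it sets out to measure. The exclusion block comes first and is free of carry-over from inclusion. A reader might also take it that the inclusion ratings come immediately after exclusion, or that the scenario task precedes Cyberball; the visible text says neither.

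**Conclusion.** The point holds for two of the three interpretation-bias components. With the fixed order, a LOC–HCG difference on them is true bias plus any residual exclusion reaction, and the planned between-group analysis cannot separate the two. This follows from the stated order and the article's own predictions, whatever pause the missing figure may show.

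For body dissatisfaction and urge to eat the point is narrower. If they are rated only after the inclusion game, as the text suggests, they cannot be attributed to exclusion alone.

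The size is unknown. With no true bias, 26 per group and d = 0.8 during exclusion, the false-declaration rate would be about 6%, 11% or 29% for assumed carry-over of 10%, 25% or 50%. The issue limits what one Study 2 hypothesis, and part of another, can show. It does not touch the sample size, the exclusion-phase comparison or the randomised Study 3. It is worth correcting because the correction is cheap.

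**What to change.** Keep the order and change the claims and test points.

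1. Restate the two inclusion-phase measures as perception of inclusion following exclusion. Do not report them as interpretation bias independent of the first Study 2 hypothesis.
2. Take and test body dissatisfaction and urge to eat at the end of the exclusion block, before inclusion starts. Describe later ratings as recovery after exclusion and re-inclusion.
3. Rest any claim of unprimed interpretation bias on the ambiguous-scenario task, and state that it is given before Cyberball. If it is now given later, it would have to be moved for this purpose.
4. Use adjustment for end-of-exclusion affect or need threat only as a sensitivity analysis. That state is measured after exposure and is predicted to differ by group, so adjusting for it may remove part of the RS-related difference of interest. It may also leave some carry-over in place.

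The cost is a narrower claim for the inclusion-phase measures and possibly one more short rating.

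Counterbalancing would be the direct design solution but is expensive. Using only inclusion data from participants who play it first leaves 13 per group, with power 0.50 at d = 0.8. Restoring 0.80 needs 4 × 26 = 104 evaluable participants, and 104 / 0.87 = 119.5, so 120 recruited.

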**Fig. 4 Fig4:**
[figure not shown]
Experimental procedure during Cyberball-task in virtual reality, VR

#### Online self-help treatment for LOC

Based on our previous work in BED in adults [49, 50] and based on our preliminary results of the blended treatment in our pilot BEAT study (active treatment consisting of 3 face to face sessions and 6 weekly e-mail guided self-help sessions, followed by 1, 3, 6, and 12-month follow-up sessions), we developed an online self-help treatment consisting of two distinct modules CBT-E and INTER-E (see Table 1). To increase compliance and decrease dropouts, therapists provide guidance via an Email generated system within the online platform [51]. Therapists (psychologists attending a post graduate training in CBT psychotherapy) will be trained and regularly supervised by SM.

**Table 1 Tab1:** Content of CBT-E and INTER-E treatment modules

0. Motivation & Psychoeducation: Short (20 min) introduction and welcome session of the i-BEAT treatment trial	
Advocatus Diaboli	
Introduction of main aspects (e.g., binge eating, emotion regulation)	
Introduction of the protagonists	
Explanation of the i-BEAT online platform	
Cognitive behavioral treatment (CBT-E)	Interpersonal emotion regulation (INTER-E)
1. Motivation & Psychoeducation	1. Motivation & Psychoeducation
Psychoeducation: What is a healthy, balanced diet?	Psychoeducation: emotion regulation, rejection sensitivity
Introduction of the meal plan	Introduction of the interpersonal emotion regulation model
Introduction of self-observation-protocols	Self-report of social rejection and rejection sensitivity episodes
2. Personal goal setting and ABC model	2. Relaxation & Non-judgmental perception
Goal analysis and goal attainment scale	Personal vicious circle of negative emotions
Introduction of the ABC model of binge eating episodes (video)	Introduction of different strategies to overcome this vicious circle
	Progressive muscle relaxation (video)
	Non-judgmental perception of negative emotions
3. The vicious circle of binge eating & PPP	3. Acceptance & Emotional tolerance
Individual vicious circle model	Personal vicious circle of negative emotions
predisposing factors, precipitating factors and	Introduction of different strategies to overcome this vicious circle
perpetuating factors	Acceptance of negative emotions
	Tolerance of negative emotions (video)
4. Craving & Strategies	4. Analysis of triggers & Maintenance factors
The craving curve	Self-report and analysis of negative emotions, interpersonal conflicts and rejection sensitivity
Symptom management: introduction of stimuli and	Identification of risk situations
reaction control strategies; create and apply	
corresponding emergency cards	
5. Cognitions	5. Effective self-support in interpersonal conflicts
Introduction concept dysfunctional thoughts	Role of emotion regulation in interpersonal conflict situations (audio)
Strategies to cope with dysfunctional thoughts:	Coping with negative emotions, interpersonal conflicts and rejection sensitivity
Defusion (audio)	
accept difficulties as part of behavioral change	
6. Setting up and relapse prevention:	6. Coping with negative emotions, interpersonal conflicts & rejection sensitivity
Identify high-risk situations, plan coping strategies,	Evaluation of self-observations with respect to emotion regulation and rejection sensitivity
adapt emergency cards	Analysis of experiences with emotion regulation strategies
score goal attainment on scale, adapt goal or set	Identifying a top 3 of the therapy content
new goals	
Identifying a top 3 of the therapy content	
13./14.: 3–month follow-up & 6-month follow-up booster sessions	
Repetition of core elements of both treatment trials: CBT-E and INTER-E	
15./16.: 2 optional 2 CBT-E sessions assigned in individual cases with more pronounced compensatory behaviour after both i-BEAT modules	

*CBT-E* cognitive behavioural therapy for eating disorders, *INTER-E* interpersonal psychotherapy for eating disorders

### Outcome measures

Data assessors are trained and supervised in diagnostics, application of experimental procedures of study 1–2. The time schedule of the data assessment during i-BEAT studies is presented in Fig. 2.

### Diagnostic assessment

Body weight and height are self-reported in study 1 and measured upon arrival for study 2 in light clothing to compute BMI (kg/m^2^). The diagnostic interview according to DSM-5, "Diagnostisches Interview bei Psychischen Störungen" (DIPS; [52]) is applied to identify mental disorders and LOC criteria, which are further confirmed via the Eating Disorder Examination Questionnaire (EDE-Q, German version; [53]). Frequency and severity of LOC or binge eating episodes are measured using the self-constructed weekly binge eating questionnaire (WBQ; [50, 54]). Measures and assessment time points during the i-BEAT study are presented in Fig. 2. In study 3, besides pre to post and follow-up measurements, the treatment process is assessed by weekly online questionnaires provided via the platform encompassing the primary outcomes frequency and severity of weekly LOC episodes, weekly interpersonal emotion regulation problems/ RS as well as attrition, adherence, dropouts, acceptance and feasibility.

### Data analysis

Data will be analyzed with the Statistical Package of Social Sciences (SPSS) and R. We will apply multiple regression models including covariates and testing specific predictors (study 1), multilevel models including moderators (App based study 1), between subjects analysis of covariance including moderators (study 2) and mixed between and within subjects analysis of covariance or linear mixed models (study 3). Exploratory epigenetic goals involve predictors and within-subject effects. Expected dropouts are assumed to amount up to 10–18%. Random occurrence should lead to equal distribution of dropouts in the different groups (LOC vs. HCG; CBT-E first vs. INTER-E first). However, in the case of an unequal distribution of the number of participants to the different groups, this issue will be addressed with multi-level models. Multi-level models are assumed to be robust against violations of equal group sizes [55]. Additionally, we will test whether a missing at random pattern is a reasonable assumption with respect to dropout.

## Discussion

The overarching goal of this project is to better understand the role of interpersonal emotion regulation problems, especially when feeling rejected (RS), in youth suffering from LOC. LOC importantly promotes EDs, general psychopathology and interferes with the development of a positive identity and the capability to engage in meaningful relationships. The interventional part of the project will show how youth accepts, reacts to and benefits from a CBT-E and an INTER-E module and whether there are specific and additive effects. The i-BEAT study represents a multi-method approach including psychological, behavioral, psychophysiological and epigenetic data, which is unique in the field and generates interdisciplinary evidence.

### List of abbreviations and questionnaire sources

Adapted German version of the Sociocultural Attitudes Towards Appearance Questionnaire, [56].Adapted German version of the Thought Shape Fusion questionnaire (TSF-B; [57]).Adapted Rejection Sensitivity Questionnaire (RSquest, adapted from the RSQ, [58]; CRSQ, German version, FZE-K, [59]).Adapted version of the Brief Mood Scale, Three-dimensional Affect Scale, [61].Adapted Working Alliance Inventory (WAI-SR; [62]).Ambiguous Scenario-Sentence Completion Task; Cognitive Bias Modification-Interpretation (rejectbias; according to [63]).App-based adapted Three Dimensions Affect scale (AppNegaff; [61, 64]).App-based adapted Visual Analog Scale Body Image Satisfaction (AppBD; [64]).Rejection Sensitivity Qu [60]).Autonomic Nervous System (ANS).Barratt Impulsiveness Scale (BIS-15; [65]).Beck Depression Inventory Fast Screen German (BDI-FS; [66]).Binge Eating Adolescents and young adults Training (i-BEAT).Binge Eating Disorder (BED).Body Mass Index (BMI).Body Shape Questionnaire (BSQ; [67]).Brief Mood Scale (BMS; [64]).CBT for eating disorders (CBT-E)..Clinical Global Impression scale (CGI; [68]).Cognitive Behavioral Therapy (CBT).Diagnostic and Statistical Manual of Mental Disorders (DSM-5).Dialectic Behavioral Therapy (DBT).Diagnostisches Interview bei Psychischen Störungen (DIPS).Difficulties in Emotion Regulation Scale (DERS; [69]).Difficulties in Emotion Regulation Scale—Short Form (DERS-SF; [70]).DNA methylation (DNAm).Dutch Eating Behavior Questionnaire (DEBQ; German version; [71]).Eating Disorder Examination- Questionnaire Kurzversion (EDE-Q8; [53]).Eating Disorder(s) ED(s).EmoReg weekly - Self-developed and adapted from the DERS ([69]), the TAS-20 [72], the H-FERS [73] and the TOMS [74].Final evaluation of the online-therapy; self-developed items (Therapeut*innen Fragebogen).Food Craving Questionnaire (FCQ; [75]).Gamified Stop Signal Task (gSST).Healthy Control Group (HCG).Heart Rate Variability (HRV).Heidelberger Fragebogen zur Erfassung von Emotionsregulationsstrategien (H-FERS; [73]).Igroup Presence Questionnaire (IPQ; [76]).Illusion of Virtual Body Ownership Scale (IVBO; [77]).Inventar zur Erfassung negativer Effekte von Psychotherpie (INEP; [78]).Interpersonal Emotion Regulation module for eating disorders (INTER-E).Inter-Personal Therapy (IPT).Loss Of Control eating (LOC).Modified version of the Weekly Binges Questionnaire (wLOC, AppLOC, AppUrge, WBQ; [79]).Need Threat Scale (NTS; [80]).Patient Health Questionnaire for Depression and Anxiety (PHQ-4; [81]).Perception of Teasing Scale (POTS; [82]).Questionnaire on frequency and intensity of rejection experiences and bullying (reject; adapted from [83, 84]).RS interpretation bias: Visual Analogue Scale of misinterpretation of being excluded in the Cyberball game (exclmisinterpret; [85]).Rejection sensitivity, RS.RS interpretation bias: Visual Analogue Scale of misinterpretation of being included in the Cyberball game (inclmisinterpret; [85]).Short version of the Social Phobia Scale (SPS; [86]).Simulator Sickness Questionniare (SSQ; [87]).Social Interaction Anxiety Scale (SIAS; [86]).Sociodemographic items (self-developed items).Standard Protocol Items for Randomized Trials (SPIRIT).State-Trait Anxiety Inventory, short-version (STAI; [88]).Stop Signal Task, (vrSSRT, SSRT; [89]).Tanner questionnaire (Tanner; [90]).Tolerance of Mood States Scale (TOMS; [74]).Translated and adapted Social Presence Survey (SPSurvey; [91]).UPPS Impulsive Behaviour Scale (UPPS; [92]).Virtual Reality (VR).Visual Analog Scale Body Image Satisfaction (VASBD; [64]).Visual Analog Scale - distress photo (distressphoto; self-developed items).Visual Analog Scale - rejection (rejectphoto; self-developed items).Visual Analog Scale - urge to eat (VASurge; self-developed items based on [93]).Weekly Binges Questionnaire (WBQ; [79]).
